### Power calculation

We expect to reduce the absolute risk of suffering from a complication by 5% by implementing the intervention programme, with a standard deviation of 10%. With an alpha of 0.05 and a power of 80% there should be 64 participants in every intervention group and in the control group. The aim is to include 80 patients into every intervention group to compensate for possible drop-out during the follow-up phase of the study. The total number of patients included in the four different intervention groups will then be 320. In addition, 80 patients will be included into the control group.

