### Aim and research questions

The aim of this randomised controlled trial (RCT) is to evaluate the effectiveness of a patient safety intervention programme for elderly hip fracture patients. Therefore, the following research questions will be addressed:

1. What is the nature and scale of adverse events and avoidable harm in the care chain for elderly hip fracture patients?

2. How is it, in the total care chain of elderly hip fracture patients, possible to reduce risks and unintended harm, and to ensure that complex care processes proceed more safely? This research question is divided into sub-questions for the three interventions:

a What is the effectiveness of the SBAR communication tool on unintended events and avoidable harm during hospital stay? (Intervention A)

b What is the effectiveness of a patient safety card with guidelines for patients and their families on signalling errors and patient trust in health care? (Intervention B)

c What is the effectiveness of evidence based bundles with regard to unintended events in the period after discharge? (Intervention C)

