## Methods/Design

### Study design

This RCT is set up as a multi-centre intervention study in which hip fracture patients aged 65 years and older will be included. Surgical wards of three hospitals will participate in the intervention groups; one surgical ward in another hospital will serve as a control group. The patients in the control group receive care as usual. A baseline measurement using a retrospective record review study will be conducted. In the following RCT the effects of three different interventions will be compared to usual care, randomisation is at patient level. Within the three intervention wards patients are randomly assigned to one of four intervention groups. The groups will receive the following interventions:

• Group 1: use of SBAR communication tool for nurses in the surgical wards

• Group 2: SBAR and patient safety card

• Group 3: SBAR and information leaflet (bundles) for after discharge

• Group 4: SBAR, patient safety card and information leaflet (bundles) for after discharge

During the study period the morning rounds will be observed once a month in each intervention ward to look at the information transfer and communication between care providers. Two weeks and six months after discharge patients will be interviewed about their recovery and the added value of the interventions. Six months after discharge the records of the included patients will be reviewed to detect possible adverse events and unintended harm. Figure 1 gives an overview of the inclusion and data collection.

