### Randomisation

In this study surgical wards in three different intervention hospitals and one surgical ward in a control hospital will participate. The eligible patients in the intervention wards will be randomly assigned to one of four intervention groups. Since the SBAR tool cannot be randomised on patient level due to practical reasons, this intervention will concern all patients in the intervention wards. Before the start of the inclusion all Informed Consent Forms and intervention materials will be assigned a unique study number. The study numbers are equally divided over four intervention groups, to ensure equal group sizes as much as possible. All materials for each individual number will be gathered and put into an envelope; the stack of envelopes will be kept in the ward in consecutive order of the study numbers. Each time an eligible patient can be asked to participate, the first envelope of the stack will be used. The process of randomisation is also shown in Figure 2.

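### One whole-programme effect size is used to size every group, although only group 4 receives the whole programme; on complications the card and leaflet contrasts cannot both have 80% power

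*Protocol article*

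**What the plan says.** The Power calculation section gives one effect size and one spread: "We expect to reduce the absolute risk of suffering from a complication by 5% by implementing the intervention programme, with a standard deviation of 10" per cent. It continues: "With an alpha of 0.05 and a power of 80% there should be 64 participants in every intervention group and in the control group". Recruitment is then raised: "The aim is to include 80 patients into every intervention group to compensate for possible drop-out during the follow-up phase of the study". This makes 320 patients in the intervention wards, and a further 80 controls.

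The Background describes the programme as the three interventions combined. Under Study design, group 1 receives SBAR alone, group 2 SBAR and card, group 3 SBAR and leaflet, and group 4 all three. That section also says that "the effects of three different interventions will be compared to usual care, randomisation is at patient level". Under Randomisation, SBAR cannot be allocated by patient, so "this intervention will concern all patients in the intervention wards". Usual care comes from one ward in a different hospital.

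The research questions separate the components: 2a for SBAR, 2b for the card and 2c for the leaflet. The last of these begins: "What is the effectiveness of evidence based bundles with regard to unintended events in the period after discharge? (Intervention C").

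**The concern.** The 5 points are expected from the full programme. Of the ten pairs that five groups can form, only group 4 v control differs by all three components; the other nine differ by one or two. Yet the size derived from those 5 points is required in all five groups, with no statement of which comparison it serves.

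This matters because the card and leaflet contrasts are the only randomised ones: SBAR is given to whole wards, and control is another hospital. A reader could take the 80% to cover comparisons that see only part of the 5 points, and so read too much into a null result on complications.

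**Working it through.** **Inputs** (Power calculation section): difference 5 points, SD 10, alpha 0.05, power 80%. Sidedness is not stated; two-sided reproduces the plan, while one-sided gives 50.

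**Reproducing the plan.** n = 2(1.960 + 0.842)² / (5/10)² = 2 × 7.849 / 0.25 = 62.8, so 63 by the normal approximation. The t-test version gives 63.8, so 64. Power at 64 v 64 is 80.1%. The target of 80 allows for 20% drop-out: 64 / 0.80 = 80.

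**What the randomised contrasts can share.** Let g1 to g4 be each group's reduction in complication risk against usual care.

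- Card effect = [(g2 + g4) − (g1 + g3)] / 2
- Leaflet effect = [(g3 + g4) − (g1 + g2)] / 2
- Sum = g4 − g1 = 5 − (SBAR's own effect)

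This identity holds whatever the interaction between card and leaflet. If SBAR is not harmful, the sum is at most 5.

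**What each contrast needs for 80% power**, keeping SD 10: difference = 10 × 2.802 × √(2/n).

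- 128 per side (two groups of 64): 10 × 2.802 × 0.125 = 3.5 points. Two of these make 7.0.
- 160 per side (two groups of 80, no loss): 10 × 2.802 × 0.1118 = 3.1 points. Two of these make 6.3.

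Both sums exceed 5. If one contrast takes 3.5 points at 128 per side, at most 1.5 are left for the other, which then has about 22% power.

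**Power under assumed splits** (t-test, two-sided 0.05, SD 10). The protocol gives no component effects, so these are illustrations.

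| Difference | 64 v 64 | 80 v 80 | 128 v 128 | 160 v 160 |
|---|---|---|---|---|
| 5 points (all three components) | 80% | 88% | – | – |
| 3.33 (two of three equal shares) | 46% | 55% | – | – |
| 2.5 (SBAR zero, card and leaflet equal) | 29% | 35% | 51% | 61% |
| 1.67 (one of three equal shares) | 15% | 18% | 26% | 32% |

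With equal shares, group 1 v control is on the last row, and groups 2 and 3 v control are on the second.

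**Why the SD cannot be carried into the correction.** Suffering a complication is a yes/no outcome, with SD √(p(1 − p)). An SD of 10% requires p(1 − p) = 0.01, so p is about 1% or 99%. A 5-point fall from 1% is impossible. A fall from 99% to 94% would itself move the SD to √(0.94 × 0.06) = 24%. The protocol gives no complication rate, so I assumed a range for the comparison side (normal approximation for two proportions, pooled variance under the null):

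| Assumed rate | SD | Power for 5 points, 64 v 64 | Detectable at 80%, 128 per side | Detectable at 80%, 160 per side |
|---|---|---|---|---|
| 10% | 30% | 19% | 8.2 points | 7.5 points |
| 20% | 40% | 11% | 12.1 | 11.0 |
| 30% | 46% | 9% | 14.6 | 13.2 |
| 40% | 49% | 8% | 16.2 | 14.6 |
| 50% | 50% | 8% | 17.2 | 15.4 |

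**The case against.** A reader might infer that the protocol claims 80% power for the card and leaflet contrasts and that this claim is false. The documents do not support that. The Power calculation section names neither contrast, and the General data collection section says the second record review is meant to assess the complete programme. Read as sizing for the whole programme alone, 64 agrees with its own inputs. What stands is that the section never says so, and that it spreads the number over groups which do not receive the programme. Pooling groups 1 to 4 against control does not restore the 5 points: with equal shares the average is (1.67 + 3.33 + 3.33 + 5) / 4 = 3.3.

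A reader might also conclude that question 2b as a whole lacks power. It asks about signalling errors and trust, which the sizing does not address. Where the evaluation of the card turns to complications and adverse events, it compares them with the baseline measurement. Question 2c overlaps more with the sized outcome, but only for the period after discharge.

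The component percentages rest on splits that I assumed. The finding that both contrasts cannot reach 80% does not: it needs only a non-harmful SBAR effect. Simple pairs (group 2 v 1 and group 3 v 1) could each show 5 points if card and leaflet were fully redundant and SBAR did nothing. That would be at odds with the protocol's argument, under Strengths and limitations, that the interventions address different aspects of care and may have more impact together.

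An analysis plan may well say which contrasts are exploratory, and its absence here is no fault. The power statement, however, is fixed in this document.

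**Conclusion.** The concern holds in limited form. One whole-programme effect size is applied to all groups, while only group 4 v control carries that contrast. Accepting 5 points, SD 10 and a non-harmful SBAR effect, the pooled card and leaflet contrasts cannot both have 80% power on complications. Power is 51% to 61% each with an even split and no SBAR effect, and 26% to 32% with equal thirds. The point bears on complications, and chiefly on question 2c.

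It would be wrong to conclude that group 4 v control does have its 80%. With the variance of a yes/no outcome, 64 v 64 has about 19% down to 8% power for 5 points at assumed control rates of 10% to 50%. That variance error is separate and larger; the mismatch described here would remain after it was corrected. That a null card or leaflet result would be misread is a risk, not something the protocol says.

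**What to change.** In the Power calculation section:

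- Name the comparison to which the sizing refers: the full programme (group 4) v usual care. Do not attach 80% to every intervention group or to component comparisons.
- For card and leaflet effects on complications, use the pooled contrasts, groups 2+4 v 1+3 and groups 3+4 v 1+2. Describe single-component pairwise comparisons as exploratory.
- Replace the SD of 10% with the binomial variance at a stated control complication rate, and give the power or detectable difference for each contrast. For assumed rates of 10% to 50%, the detectable difference is roughly 8 to 17 points at 128 per side and 8 to 15 points at 160 per side. Do not print the 3.5 and 3.1 points as the trial's detectable differences, and do not reaffirm 80% for group 4 v control.

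The cost is wording and a short recalculation, with a less favourable power statement. Enrolment and data collection are unchanged.

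### The sample size treats a yes/no complication risk as a continuous measure with a standard deviation of 10%, so 64 per group does not give the stated 80% power

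*Protocol article*

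**What the plan says.** The Power calculation section names one effect, for one outcome. The trial is expected to "reduce the absolute risk of suffering from a complication by 5% by implementing the intervention programme, with a standard deviation of 10" per cent. It continues: "With an alpha of 0.05 and a power of 80% there should be 64 participants in every intervention group and in the control group". Recruitment is raised to allow for loss to follow-up: "The aim is to include 80 patients into every intervention group to compensate for possible drop-out". The comparison ward is sized in the same way: "In addition, 80 patients will be included into the control group". No complication rate is given for either arm, and the sidedness of the test is not stated.

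Elsewhere, Outcome measures lists the incidence of complications and adverse events first among the primary outcomes. Data analysis bases the reliability statistic on whether complications and adverse events are present or absent. It also says that both an incidence and a mean number will be calculated.

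**The concern.** A difference in risk between two groups of patients is a difference between two proportions. Its precision depends on the two risks, and there is no separate standard deviation to choose. The article gives a standard deviation and omits the risk, which is the input that the calculation needs.

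The 80% power statement is the only justification offered for the trial's size. If it is wrong, a non-significant complication result could be read as evidence that the programme does not work, when the trial was unlikely to detect the effect it was planned around. A significant result at low power would, on average, exaggerate the true effect if that effect is near 5 points.

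**Working it through.** **1. Inputs from Power calculation.** Absolute reduction 5 points, standard deviation 10%, alpha 0.05, power 80%, 64 per group (80 recruited).

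**2. Reproducing the plan's figure.** Treat the outcome as continuous: d = 5/10 = 0.5. The normal formula n = 2(1.960 + 0.842)²/d² gives 2 × 7.849/0.25 = 62.8, so 63. The two-sample t-test version gives 63.8, so 64, which is the plan's number. A one-sided test gives 50 and does not match. The calculation is therefore a two-sided comparison of means.

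**3. Are the inputs compatible with a yes/no outcome?** For a yes/no outcome, SD = √(p(1 − p)). Setting this to 0.10 gives p(1 − p) = 0.01, so p = 0.0101 (or 0.9899). A risk of 1.0% cannot fall by 5 points. At risks of 10%, 20%, 30% and 50% the SD is 0.30, 0.40, 0.46 and 0.50, which is three to five times the value used.

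**4. Recalculation with two proportions.** The control risk p is not in the document, so it is *assumed* over 10% to 50%. The intervention risk is q = p − 0.05. With n per group and p̄ the mean of p and q:

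power = Φ[(0.05 − 1.96·√(2p̄(1 − p̄)/n)) / √((p(1 − p) + q(1 − q))/n)]

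Example for p = 0.30, n = 64: p̄ = 0.275. The null standard error is √(2 × 0.275 × 0.725/64) = 0.0789. The alternative standard error is √((0.21 + 0.1875)/64) = 0.0788. Power = Φ[(0.05 − 0.1547)/0.0788] = Φ(−1.33) = 9.2%.

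| Assumed control risk | Power, 64 v 64 | Power, 80 v 80 (no drop-out) | Power, pooled 256 v 64 | n per group for 80% |
|---|---|---|---|---|
| 10% | 18.7% | 22.3% | 35.3% | 435 |
| 20% | 11.2% | 12.9% | 17.9% | 906 |
| 30% | 9.2% | 10.5% | 13.4% | 1,251 |
| 50% | 8.1% | 9.2% | 10.8% | 1,565 |

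These count rejections in the correct direction only; counting both tails adds less than 1 point at 64 v 64. Exact enumeration of the chi-square test at 64 v 64 agrees: 18.7%, 11.1%, 9.9% and 8.1%.

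**5. Most favourable case.** The smallest control risk that allows a 5-point drop is 5% falling to 0%. At 64 v 64 that gives 44% (40% by exact enumeration), and 152 per group would be needed.

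**6. What the planned size can detect with 80% power.**

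| Assumed control risk | 64 v 64 | 128 v 128 (card or leaflet, yes v no) |
|---|---|---|
| 10% | none: 10% falling to 0% gives about 74% power | about 8 points |
| 20% | about 16 points | about 12 points |
| 30% | about 20 points | about 15 points |
| 50% | about 24 points | about 17 points |

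The 128 comes from two of the four intervention groups at 64 each.

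**The case against.** *The calculation was for the mean number of complications.* Data analysis does mention a mean number. But the Power calculation section speaks of the absolute risk of suffering a complication, which is a proportion. This does not rescue the figure.

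*The intended contrast is the whole programme against usual care.* This is a plausible reading, since the expected reduction is tied to the programme and the second record review is meant to assess the complete programme. Pooling does help: about 35% power at 10% risk with 256 v 64, and about 41% if all 320 v 80 are retained. At 30% risk it is 13% and 16%. This part of the objection stands, and the pooled figures belong beside the per-group ones. However, the article attaches its claim to each group ("there should be 64 participants in every intervention group and in the control group"), and the pooled contrast remains far below 80% over the assumed range.

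*Complications will also be compared with the 2007 baseline.* They will, according to the evaluation of the patient safety card. Each ward must treat at least 100 such patients a year. Assuming about 300 baseline records from the three intervention wards against 320 trial patients, power for a 5-point drop is about 66%, 37%, 29% and 24% at risks of 10%, 20%, 30% and 50%. That is better, but it is a non-randomised before-after comparison and still short of 80%. A reader might infer that the trial has almost no power for any comparison. The documents do not support that, because the very low figures belong to 64 v 64.

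*A journal article condenses the full protocol.* True, but the problem here is a definite statement whose inputs contradict each other, and no missing detail would repair it.

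**Conclusion.** Wrong as written. The contradiction lies within the Power calculation section and needs no outside figure: the stated standard deviation is incompatible with a 5-point fall in a risk, and 64 per group follows only from a comparison of means. At 64 v 64 no control risk brings a 5-point reduction near 80% power; the ceiling is about 44%, at 5% v 0%.

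The size of the shortfall rests on assumptions: a control risk between 10% and 50%, a two-sided test at 0.05, equal groups, and no allowance for clustering by ward or multiple comparisons. A reader might take roughly 8% to 19% as the trial's actual power. The documents do not support it as a fact, because they give no complication risk for hip fracture patients. The nearest figure, in Background, is 9.2% for adverse events over all hospital admissions, which is a different outcome and population. Used only as an illustration, it gives 20% at 64 v 64.

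Nor does it follow that any significant result must overstate the effect. Exaggeration is expected on average if the true effect is near 5 points, but the true effect could be larger.

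**What to change.** Keep the planned enrolment and replace the power statement.

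- Take the control risk of a complication from the 2007 baseline record review, which already has the rate of complications as a main outcome.
- Use the two-proportion formula, and state whether the test is two-sided.
- Give the power for a 5-point reduction and the difference detectable with 80% power under the *same* assumed risk. Do this for the single-group contrast (64 v 64), the card and leaflet contrasts (128 v 128) and the pooled programme contrast (256 v 64).
- Until the baseline risk is known, show the range of risks and do not quote a single figure.
- Report the complication effect as a risk difference with a 95% confidence interval, and state that a non-significant result does not exclude a 5-point benefit.

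The 64 per group should not be re-attached to functional mobility. A half-standard-deviation effect might seem to suit a continuous score, but the article gives no effect size or standard deviation for mobility, so this would be a justification made after the fact.

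The cost is a rewritten paragraph and a much less favourable stated power. No additional patients or data collection are needed.

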### Data analysis

The data will be analysed using Stata 10.1 for Windows. During the data collection regular data checks (identify out-of-range answers, inconsistent responses and missing data) will be performed.

In the evaluation of the effectiveness of the intervention programme all analyses will be performed at patient and group level. The data will be analysed using the intention-to-treat principle. This means that patients will remain in the group to which they were randomly allocated at baseline. The patient characteristics will be compared for all groups and, if necessary, we will correct for differences.

The determination of complications is based on the complication registration of the Dutch Society of Medical Specialists (in Dutch: Orde van Medisch Specialisten). The determination of adverse events is based on three criteria; 1) an unintended (physical and/or mental) injury which 2) results in temporary or permanent disability, death or prolongation of hospital stay, and is 3) caused by health care management rather than the patient's disease. To determine whether the injury is caused by health care a six-point scale will be used, causation scores of 4-6 will be classified as adverse events. The preventability of the adverse events will also be measured on a six-point scale, scores of 4-6 will be classified as preventable adverse events. The incidence and mean number of complications and adverse events will be calculated.

The inter-rater reliability of the review process will be expressed as a kappa statistic. This kappa statistic will be calculated for the determination of the presence or absence of complications and adverse events. The records from the reliability study will be used for this analysis, they represent up to 10% of all reviewed patient records.

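### The 64 per group assumes independent patients, but every comparison with the control group is three wards against one, so the stated 5% alpha and 80% power hold there only if the ICC is essentially zero

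*Protocol article*

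**What the plan says.** All references are to the protocol article.

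- **Power calculation.** The target is the effect of the programme: "We expect to reduce the absolute risk of suffering from a complication by 5% by implementing the intervention programme", "with a standard deviation of 10"%. The section concludes: "With an alpha of 0.05 and a power of 80% there should be 64 participants in every intervention group and in the control group". The increase from 64 to 80 per group is attributed to drop-out only, giving 320 intervention patients and 80 controls. No ICC, design effect or ward term appears.
- **Study design.** Three surgical wards in three hospitals deliver the interventions, and "one surgical ward in another hospital will serve as a control group". Patients are randomised among Groups 1 to 4 inside the three intervention wards. None is randomised to control.
- **Randomisation.** "Since the SBAR tool cannot be randomised on patient level due to practical reasons, this intervention will concern all patients in the intervention wards". The Implementation text for Intervention A repeats that SBAR applies to all hip fracture patients admitted there during the research period.
- **Data analysis.** "all analyses will be performed at patient and group level", by intention to treat, with correction for patient characteristics where needed. No model is named.

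**The concern.** The safety card and the leaflet are allocated patient by patient within wards, so a patient-level comparison suits them. SBAR has no concurrent comparator except the control ward. Any single intervention group, or the programme as a whole, set against usual care is also a contrast of three wards with one. Patients in one ward share surgeons, nurses, protocols and record keeping, so 80 patients from one ward carry less information about usual care in general than 80 independent patients would.

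The power section nevertheless sizes exactly this contrast with the independent-patient formula. If the result is then tested as though patients were independent, the standard error is too small, and an ordinary difference between wards can be read as a programme effect on a primary outcome. Recruiting more patients per ward does not cure this, because the part of the variance due to the single control ward does not shrink.

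**Working it through.** **Inputs from the article.** Difference 5%, SD 10%, so d = 0.5; alpha 0.05; power 80%; 64 (80) per group; pooled 320 v 80; three wards v one. Sidedness is not stated. Two-sided is assumed, because a one-sided calculation gives 50 per group, not 64.

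**Assumption.** The article gives no ICC. Values from 0.005 to 0.05 are used.

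**1. Reproduce the stated figure.** A two-sided two-sample t-test with d = 0.5, alpha 0.05 and power 0.80 needs 63.8, i.e. 64 per group (63 by the normal formula). The stated 64 is therefore the figure for independent patients, with a design effect of 1.

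**2. Variance of the control comparison.** In units of the outcome variance, for a post-only comparison with patients spread evenly over the three wards:

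- independent patients: V0 = 1/n1 + 1/n0
- three wards v one: V = (1 − ICC)(1/n1 + 1/n0) + ICC(1/3 + 1)
- true alpha of the unadjusted test: 2[1 − Φ(1.96/√(V/V0))]
- power at a true 5% level, ICC known: Φ(0.5/√V − 1.96)

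Example, 64 v 64 at ICC 0.01: V0 = 2/64 = 0.03125; V = 0.99 × 0.03125 + 0.01 × 1.3333 = 0.0443; V/V0 = 1.42. True alpha = 2[1 − Φ(1.647)] = 10.0%. Power = Φ(2.376 − 1.96) = 66%.

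| Comparison | ICC | V/V0 | True alpha | Power, ICC known |
|---|---|---|---|---|
| 64 v 64 | 0 | 1.00 | 5.0% | 81% |
| 64 v 64 | 0.005 | 1.21 | 7.5% | 73% |
| 64 v 64 | 0.01 | 1.42 | 10.0% | 66% |
| 64 v 64 | 0.05 | 3.08 | 26% | 36% |
| 80 v 80 | 0.005 | 1.26 | 8.1% | 80% |
| 80 v 80 | 0.05 | 3.62 | 30% | 38% |
| 320 v 80 | 0.01 | 1.84 | 15% | 84% |
| 320 v 80 | 0.05 | 5.22 | 39% | 42% |

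Simulation of the unadjusted t-test (20,000 trials per setting) agrees: 10.0% and 27.3% for 64 v 64 at ICC 0.01 and 0.05, and 15.0% and 39.9% for 320 v 80.

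**3. Floor.** With d = 0.5, 80% power needs V ≤ [0.5/(1.960 + 0.842)]² = 0.0319. The ward term alone is ICC × 4/3, so the requirement cannot be met once ICC exceeds 0.0319 × 3/4 = 0.024. Below that, n per group = 2(1 − ICC)/(0.0319 − ICC × 4/3), which is about 80, 107 and 379 at ICC 0.005, 0.01 and 0.02.

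**4. ICC not known.** The power figures above are optimistic. A test on ward means with 2 degrees of freedom has, for 64 v 64, about 36% power even at ICC 0, 28% at 0.01 and 16% at 0.05.

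**5. Using the 2007 baseline.** For a change from baseline, the ward term becomes 2 × ICC(1 − r) × 4/3, where r is the correlation of a ward's level between periods. Assume ICC 0.05, 80 v 80, and 80 baseline records per ward (80 control, 240 intervention). Then V0 = 0.025 + 1/80 + 1/240 = 0.0417. At r = 0.9, V = 0.95 × 0.0417 + 0.0133 = 0.0529, ratio 1.27, alpha about 8%. At r = 0.8 alpha is about 12%, and at r = 0.5 about 22%. With 100 records per ward, the figures for r = 0.8 and 0.5 are about 13% and 23%.

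**The case against.** Several points on the other side stand.

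- **The ICC is assumed.** At ICC 0 the stated figures hold. If a small ICC were known, 80 v 80 at 0.005 would still reach about 80% power, and 320 v 80 at 0.01 about 84%. A reader might infer that power falls below 80% in every case, or that 26% or 30% is this trial's false-positive rate. The documents support neither. The direction is certain, but the size is conditional.
- **The analysis is not spelled out.** A reader might infer that the article commits to ignoring ward. It does not: the Data analysis section names no model, and the Participating surgical wards section collects ward data so that wards can be compared and important differences corrected. Model detail may properly sit in a fuller plan. However, with one control ward, ward and treatment cannot be separated by covariates, and no later model makes the stated power true for this contrast.
- **A baseline exists.** The 2007 record review is meant as the reference for judging effects, and it removes ward differences that are constant over time. Ward-by-period variation remains (step 5). The baseline records also carry no cognitive exclusion, whereas the trial requires good cognition.
- **Not everything is delivered by ward.** A reader might extend the point to the card and leaflet. That would be wrong, since both are randomised by patient within wards.
- **Overlap.** With a single control ward, between-ward variance and confounding by hospital are closely related and should not be counted as two independent faults. The present point concerns the standard error and the stated power, and would remain if the wards had no systematic differences.

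**Conclusion.** The concern holds for the power statement as applied to comparisons with the control group. That part rests on explicit text: 64 is the independent-patient figure, and the contrast it is attached to is three wards against one.

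For a post-only patient-level comparison of 64 with 64, ICCs between 0.005 and 0.05 put the true alpha between about 7.5% and 26% and the known-ICC power between about 73% and 36%. These power figures take the article's d = 0.5 at face value. Whether an SD of 10% suits a yes/no complication is a separate question, and the alpha inflation does not depend on it. Baseline adjustment can shrink the problem where ward levels are stable over time, but cannot remove it with one control ward. The patient-randomised contrasts among Groups 1 to 4 are sound in this respect.

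**What to change.** **Power calculation.** State that 64 (80) per group assumes independent patients and cannot be relied on to give 80% power for any intervention group, SBAR or the programme against the control ward. Show the power for these comparisons over a stated range of ICCs. Do not transfer the 64 and 80% to the card or leaflet: the 5% is a programme effect, and each of those factors compares about 160 with 160 (two groups of 80 on each side). Their power should be stated for their own assumed effects.

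**Data analysis.** Analyse the card and leaflet at patient level with ward as a fixed effect. Report SBAR or the programme against control as exploratory, giving ward-specific changes from the 2007 baseline and intervals that include between-ward variance over the stated ICC range. Note that four wards, only one of them control, cannot estimate the ICC.

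**Cost.** Wording in two sections and a few lines of code, with no extra patients or data. The downside is wider intervals and a less favourable stated power for the programme comparison.
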